**Methods:**

The DNPM project is evaluated as a Hybrid Type 3 implementation study using a non-randomized, modified stepped-wedge design. Twenty-one university hospital sites across Germany will transition from standard, non-harmonized care to a harmonized personalized medicine intervention at different time points, based on administrative readiness indicated by certification. The primary outcome is change in patient management due to molecular tumor board (MTB) decisions, assessed on three tiers using prospectively collected primary data entered by clinical staff: (1) number of patients with access to an MTB, (2) proportion with revised diagnostic or therapeutic recommendations, and (3) proportion with implemented changes. Therefore, the study aims to include 4,807 patients (intervention group: 3.507). A mixed-methods approach is employed to evaluate further aspects of the implementation process including patient and staff satisfaction, perceived quality of care, and the degree of harmonization and collaboration within the network. Health economic outcomes include health-related quality of life, healthcare utilization costs, and intervention-related costs.

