### Sample size

The study aims to recruit a total of 4,807 patients, including 3,507 in the intervention group and 1,300 in the control group. The following assumptions underlie the sample size estimation: For nine newly established ZPMs (centers), two centers would be acceptable as dropouts. At least four existing centers in BW are considered unlikely to drop out, and seven newly initiated ZPMs serve as the basis for the sample size estimation. The new centers will contribute to controlling/intervening patients before/after initiation as ZPM, while the existing ZPM will only have intervention patients. This approach, inspired by the stepped-wedge design, has already been successfully used in several projects funded by the Innovation Fund (10). An average stay of 6 months in the control phase is assumed. It is estimated that each comprehensive cancer center (CCC) will have between 300 and 500 patients with PM, resulting conservatively in 1,300 control patients. This is compared with an estimated 3,500 ZPM patients from existing ZPM and those newly implemented during the study period. With these numbers, ignoring the cluster effect, differences of approximately 5% can be detected in the chi-squared test (Type I error 5% two-sided) with a power of >80% (exactly 86%) and differences of 7% with >90% (exactly 96%) power. Assuming a variance inflation due to cluster effects of 2, differences of 7% can still be detected with 85% power, and with very high cluster effects of 4 or 6, differences of 10% or 13% can be detected with 85% power.

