### Outcomes

A central element is the primary endpoint at the patient level (micro-level), which is divided into a three-tiered endpoint and allows conclusions about the benefits of the intervention. Tier 1 includes the frequency of access to the new form of care; Tiers 2 and 3 encompass the development and implementation of therapy proposals. The quantitative evaluation is supplemented by a quantitative patient survey using validated questionnaire instruments and a health economic assessment. In addition to quantitative data collection, interviews with patients are conducted to capture patient understanding of and expectations regarding personalized medicine. Overall, the development and enhancement of structures and processes in centers for personalized medicine (ZPM) is documented through standardized self-report questionnaires (see Appendix 2), as well as interviews and focus groups. This also specifically captures the exchange and knowledge transfer between ZPMs, as well as the extent to which an exchange of harmonized data has taken place. A complete list of the measures used in the quantitative and qualitative process evaluation, as well as secondary patient-related endpoints (clinical: response, PFS, OS, toxicity, patient questionnaires, and health economic measures), is presented in Table 2. A design diagram further elaborating on the data collection time points can be found in Appendix 3.

**Table 2 T2:** Primary and secondary endpoints and data collection.

Level	Evaluation	Primary endpoint	Time point	Instrument
Micro-level	Quantitative evaluation	Change in patient management based on the decision of the tumor board (assessed on three tiers):		Based on a quantitative questionnaire filled out by staff on site *(included in the provider questionnaire)*
		Tier 1: number of patients admitted to the tumor board	T0 = day of initial presentation at the tumor board)	
		Tier 2: proportion of patients with changed diagnostic strategy and/or therapy recommendation due to the decisions of the tumor board	T1 = day of therapy decision	
		Tier 3: proportion of patients with an actually implemented changed diagnostic strategy and/or therapy	T2 = day of the first therapeutic intervention	
		Secondary endpoints		
Micro-level	Quantitative evaluation	Clinical data of patients treated in the MTB • Response • Progression-free survival • Overall survival • Toxicities	event-driven	*Included in the provider questionnaire*

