### Data collection and management

#### Quantitative evaluation

The primary endpoint contains three tiers. At Tier 1, the primary endpoint is the number of patients who receive an indication-driven, standardized access to the new form of care—personalized diagnostics and therapy—defined as access to the MTB. For this endpoint, a standardized data collection instrument will be developed to document both the original procedure and the newly implemented one, including the extent of the changes made (e.g., additional molecular diagnostics and therapy). The new procedure will be based on predefined, evidence-based criteria established by the ZPM network in BW. At Tier 2, it will be assessed for which patients the diagnostic process or diagnostic interpretation was significantly changed. Among this group, Tier 3 evaluates the proportion of patients for whom the changes ultimately led to treatment within the framework of personalized medicine. These changes may also include recommendations for genetic counseling, which—although not directly involving therapy or additional diagnostics—represent a modification in patient care.

Secondary clinical endpoints will be assessed continuously during the study: Adverse events (AEs) and serious adverse events (SAEs) will be recorded as they occur, and overall survival (OS) and progression-free survival (PFS) will be recorded every 6 months (T4–T8) until the end of the observation period, with a minimum follow-up of 6 months and an average follow-up of 12 months.

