## Analysis and anticipated results

### Quantitative evaluation

The hierarchically organized endpoints described above (see Table 2) will be analyzed as binary variables (yes/no) while accounting for cluster effects from the individual centers using generalized estimating equations (GEE) in a logistic regression model (working correlation structure: exchangeable). The study arm (traditional procedure vs. standardized procedure according to the new form of care) will be coded as a binary variable, changing over time for centers newly included in the intervention condition. The Type I error rate will be set at 0.05 (two-sided). *P*-values for the secondary endpoints will be reported, but these should not be interpreted confirmatively. No corrections for multiple testing are necessary. Cluster effects will be addressed using GEE. In the primary analysis, we will use the independence estimation equation, and in a secondary analysis, we will use the exchangeable correlation structure within centers which allows for estimation of the cluster effect.

We expect the intervention to have a measurable impact on patient management as reflected in the primary outcome. Specifically, we anticipate the following effects across three levels of outcome assessment: Level 1, an increase in the frequency of indication-driven, standardized access to the MTB following implementation of the intervention; Level 2, a higher proportion of cases in which the recommendation for further diagnosis or therapy is modified as a result of MTB discussions under the harmonized approach; Level 3, an increase in the proportion of patients for whom the recommended changes in diagnostics or therapy are actually implemented in clinical practice. These analyses (Levels 1–3) will be additionally done with respect to the evidence level of the recommended therapies.

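### Tier 3 of the primary endpoint is restricted to Tier 2-positive patients in one section but not in Table 2 or the abstract, and the restricted version conditions on an outcome of the intervention

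*Protocol article*

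**What the plan says.** Tier 3 is described in four places.

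- **Abstract, Methods:** "3) proportion with implemented changes". No restriction to Tier 2.
- **Outcomes, Table 2:** "Tier 3: proportion of patients with an actually implemented changed diagnostic strategy and/or therapy". No restriction to Tier 2; diagnostic and therapeutic changes both count.
- **Data collection and management, Quantitative evaluation:** Tier 2 comes first, "At Tier 2, it will be assessed for which patients the diagnostic process or diagnostic interpretation was significantly changed", and then "Among this group, Tier 3 evaluates the proportion of patients for whom the changes ultimately led to treatment within the framework of personalized medicine". Here the denominator is explicitly the Tier 2-positive patients, and the numerator is treatment.
- **Analysis and anticipated results, Quantitative evaluation:** "Level 3, an increase in the proportion of patients for whom the recommended changes in diagnostics or therapy are actually implemented in clinical practice". This fits either denominator. The tiers "will be analyzed as binary variables (yes/no) while accounting for cluster effects", and the model description names no denominator.

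The same analysis section expects Tier 2 to rise under the intervention: "Level 2, a higher proportion of cases in which the recommendation for further diagnosis or therapy is modified".

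The Sample size section bases its power on 1,300 control and 3,507 intervention patients: "With these numbers, ignoring the cluster effect, differences of approximately 5% can be detected in the chi-squared test", with 86% power at a two-sided 5% level. It gives no base rate and no Tier 2 rate.

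**The concern.** Two analysts following this text could compute different primary Tier 3 results, because the denominator and the numerator both depend on which section is followed.

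The choice affects bias as well as wording. If Tier 3 is computed only among Tier 2-positive patients, the comparison is restricted by something the intervention is meant to change. The intervention group would then include patients who would not have been Tier 2-positive under control conditions, with no counterpart in the control group. The difference in implementation proportions mixes any effect on implementation with this change in who is counted. The design is already non-randomized, so this selection comes on top of any existing imbalance.

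Tier 3 is the tier closest to patient benefit. On the restricted definition, an intervention that gets more patients treated could appear to lower implementation, and one that makes fewer, more selective recommendations could appear to raise it. The power statement also describes the full sample, not the subset.

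**Working it through.** **1. Reproduce the stated power.** Inputs from Sample size: n₀ = 1,300, n₁ = 3,507, two-sided 5%, difference 5 points, no clustering. The base rate is not given; rates of 47.5% and 52.5% are assumed.

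Power = Φ[(d − 1.96·SE₀)/SE₁], where SE₀ uses the pooled proportion and SE₁ the two separate proportions.

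- Pooled proportion = (1,300 × 0.475 + 3,507 × 0.525)/4,807 = 0.5115
- SE₀ = √[0.5115 × 0.4885 × (1/1,300 + 1/3,507)] = 0.01623
- SE₁ = √[0.475 × 0.525/1,300 + 0.525 × 0.475/3,507] = 0.01622
- Power = Φ[(0.05 − 1.96 × 0.01623)/0.01622] = 86.9% (86.2% with continuity correction)

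This matches the stated 86%. The 85% for 7 points with variance inflation 2 also reproduces (86.3%). The stated figures therefore belong to the full sample at rates near 50%.

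**2. Same calculation on Tier 2-positive patients.** Multiply both group sizes by an assumed Tier 2 share q, keeping 47.5% vs 52.5%:

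| q (assumed) | Control | Intervention | Power, 5 points |
|---|---|---|---|
| 1.0 | 1,300 | 3,507 | 87% |
| 0.8 | 1,040 | 2,806 | 79% |
| 0.6 | 780 | 2,104 | 67% |
| 0.5 | 650 | 1,754 | 59% |
| 0.4 | 520 | 1,403 | 50% |
| 0.3 | 390 | 1,052 | 39% |

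The difference detectable with 86% power is about 7.0 points at q = 0.5, 7.8 at q = 0.4 and 9.0 at q = 0.3. Letting q differ between groups changes little: 40% in control and 60% in intervention (520 vs 2,104) gives 53%. For 7 points with variance inflation 2, q = 0.5 gives 58%, or 70% if the inflation shrinks with cluster size to 1 + (2 − 1) × 0.5 = 1.5.

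**3. Sensitivity to the base rate.** For 10% vs 15% with q = 0.5 (650 vs 1,754), power is 91%. On the full sample those rates give 99.7%. Power still falls, but stays above 86%.

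**4. Direction of effect.** All rates are assumed. Tier 2 is 40% in control and 60% under intervention. The 40% who are Tier 2-positive either way have changes implemented at 50% in both groups; the additional 20% at 20%.

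- All patients: control 0.40 × 0.50 = 20%; intervention 0.40 × 0.50 + 0.20 × 0.20 = 24%. Difference +4 points.
- Tier 2-positive patients: control 0.20/0.40 = 50%; intervention 0.24/0.60 = 40%. Difference −10 points.

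Nobody is worse off in this example. With the planned group sizes and no clustering, the all-patient contrast has 84% power, and the restricted contrast has 98% power to show a difference in the wrong direction.

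If the additional 20% were implemented at the same 50%, the all-patient result would be 20% vs 0.60 × 0.50 = 30%, a gain of 10 points, while the restricted result would be 50% vs 50%. The two contrasts therefore differ even when the added patients are no harder to treat; a reversal needs a lower rate among them.

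**The case against.** Only the data collection section names a denominator. Table 2 and the abstract are short labels, and the words all patients appear in neither. The Objectives speak of implementing treatment recommendations, which presupposes that one was made, and the analysis section calls the endpoints hierarchical. A consistently nested reading is therefore possible. This stands in part: the all-patient denominator is the plain reading of Table 2, not a spelled-out rule. It does not rescue the restricted rule, which is explicit and is the one that conditions on a post-intervention outcome.

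Uptake of recommendations once made is a legitimate quantity in an implementation study, and on a nested definition with one numerator the all-patient proportion equals Tier 2 times restricted Tier 3. That is a good reason to report the restricted proportion, but not to make it the primary contrast.

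Two stronger readings are tempting. A reader might infer that restricted Tier 3 simply lacks the stated power. The documents do not support that: they give no base rate, and 10% vs 15% with half the patients Tier 2-positive still gives 91%. A reader might also infer that the effect will reverse because the added patients are harder to treat. Nothing in the documents says so; the example shows only that reversal is possible.

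Finally, the set of patients presented to the tumor board may itself change, since Tier 1 expects more access. That is correct, and an all-patient denominator does not remove it.

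**Conclusion.** The concern holds as an inconsistent and, in its restricted form, poorly chosen definition of a primary tier. Denominator and numerator both differ between sections. The restricted denominator is expected, by the plan's own hypothesis, to move with the intervention, so the contrast is open to selection bias and may differ from the all-patient effect in size or sign.

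The loss of power is conditional. Near 50%, without clustering and with a Tier 2 share of 30% to 60%, power for 5 points would be about 39% to 67% instead of about 87%; at low base rates the loss is smaller. The Tier 2 shares, base rates and sign example are assumptions. The difference between the definitions and the expected rise in Tier 2 come from the protocol. Because the choice can change the primary result, it should be settled before outcome data are analysed.

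**What to change.** Define primary Tier 3 once: the proportion of all enrolled patients at first tumor board presentation with an implemented changed diagnostic strategy and/or therapy (Table 2's numerator), counting patients without a Tier 2 change as not implemented. Amend both parts of the data collection sentence to match, that is, the restriction to the Tier 2 group and the narrowing to treatment. State the same denominator in the analysis section. This definition also fits the sample on which the stated power is based.

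Report implementation among Tier 2-positive patients as a secondary, non-confirmatory measure, with a note that its denominator depends on the intervention. State as a remaining limitation that the patients presented to the tumor board may also change with the intervention (Tier 1).

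The cost is a short wording change in the protocol and any analysis plan, with no new data. The Timeline section reports recruitment complete on 30 September 2024 and data collection ending in November 2025, so the decision should be dated and recorded before outcome data are analysed.

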## Methods: participants, interventions, and outcomes

### Intervention description

All participating centers will undergo a certification process as oncological centers in accordance with the requirements set by the German Cancer Society (8). Centers will transition to the intervention group once they meet the DNPM criteria and receive a positive audit result. In the intervention group, patients will be treated according to DNPM standards, which encompass quality-assured molecular diagnostics and evidence-based treatment recommendations within interdisciplinary MTBs. The therapies initiated at these sites may vary individually in terms of timing, duration, and type.

The DNPM standards encompass ongoing quality control measures, the standardization of diagnostics, bioinformatics, MTBs, referrals for genetic counseling and imaging, and clinical decision-making based on harmonized evidence levels. See Appendix 1 for a summary of the dimensions of certification. The standardized and registered components of ZPM include a uniform and organized documentation of MTB decisions (approximately 40 harmonized parameters), coordinated clinical and genomic datasets (each containing over 200 parameters), consistent follow-up and response documentation, and a structured process for off-label treatment applications that has been agreed upon with the medical service and government health insurances. A nationwide network in the field of personalized oncology is established following these core measures:
**Micro-level:** improvement of evidence-based treatment recommendations in the MTB**Meso-level:** quality-assured, harmonized operation of ZPM (Centers for Personalized Medicine) at CCC locations**Macro-level**: establishment and use of a digitally connected PM registry (using the example of the Baden-Württemberg ZPM network) to improve treatment recommendations

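### Tiers 2 and 3 mix treatment with diagnostic and counselling changes although the objectives concern treatment only, and Tier 3 has two incompatible definitions

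*Protocol article*

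**What the plan says.** The Objectives section lists three aims for the primary analysis. The two that correspond to Tiers 2 and 3 are a greater chance of treatment recommendations and more actual implementation of them. Neither mentions diagnostics or counselling.

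The endpoint itself is wider. Table 2 (Outcomes) gives "Tier 2: proportion of patients with changed diagnostic strategy and/or therapy recommendation due to the decisions of the tumor board" and "Tier 3: proportion of patients with an actually implemented changed diagnostic strategy and/or therapy". The analysis section (Analysis and anticipated results, Quantitative evaluation) likewise names diagnostics or therapy for Levels 2 and 3.

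The data collection section (Data collection and management, Quantitative evaluation) words both tiers differently. For Tier 2: "At Tier 2, it will be assessed for which patients the diagnostic process or diagnostic interpretation was significantly changed". Then, restricted to that group, "Tier 3 evaluates the proportion of patients for whom the changes ultimately led to treatment within the framework of personalized medicine". It continues: "These changes may also include recommendations for genetic counseling", and describes these as a modification of care "although not directly involving therapy or additional diagnostics".

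The Intervention description lists among the contents of the DNPM standard "the standardization of diagnostics, bioinformatics, MTBs, referrals for genetic counseling and imaging". The Outcomes section says that the three-tier endpoint permits conclusions about the benefit of the intervention.

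**The concern.** Each tier is analysed as a yes/no variable. If a patient can score through a diagnostic change or a counselling recommendation alone, the tier no longer answers the question in the Objectives. A higher Tier 2 proportion after certification could reflect more treatment recommendations, more diagnostic or counselling changes, or both, and the analyses described do not separate these. A reader who takes the result as the answer to the treatment objectives could credit the programme with a treatment gain that did not occur.

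For Tier 3 the problem goes further. The document gives two rules for who counts and two possible denominators, so the same data can give different answers depending on which section the analyst follows.

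**Working it through.** **1. Wordings side by side**

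- Tier 2, Objectives: treatment recommendation.
- Tier 2, Table 2 and analysis section: diagnostics or therapy; either is enough.
- Tier 2, data collection section: diagnostic process or interpretation; therapy is not named, and counselling recommendations may be included as changes.
- Tier 3, Objectives: treatment recommendation implemented.
- Tier 3, Table 2 and analysis section: implemented diagnostics or therapy, as a proportion of patients with no restriction stated.
- Tier 3, data collection section: the change led to treatment, among Tier 2 patients only.

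So Tier 2 can be met without a treatment recommendation under every operational wording. Tier 3 can be met without treatment under Table 2 and the analysis section, but not under the data collection section's own definition.

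**2. The plan's own power figure**

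Inputs from the Sample size section: n1 = 1,300 control, n2 = 3,507 intervention, two-sided 5% test, 5-point difference, stated power 86%. With d = |p1 − p2| and p̄ the pooled proportion:

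power = Φ{ [d − 1.96·√(p̄(1−p̄)(1/n1+1/n2))] / √(p1(1−p1)/n1 + p2(1−p2)/n2) }

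No baseline rate is stated. Centred on 50% (47.5% vs 52.5%), this gives 86.9%, or 86.2% with continuity correction. The stated figure is reproduced.

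**3. Illustration with no treatment effect (assumed rates)**

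Assume therapy recommendations in 50% of both groups. Among the other 50%, let diagnostics-only or counselling-only changes occur in 10% (control) and 20% (intervention).

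- Control Tier 2: 0.50 + 0.50 × 0.10 = 0.55
- Intervention Tier 2: 0.50 + 0.50 × 0.20 = 0.60
- p̄ = (1,300 × 0.55 + 3,507 × 0.60)/4,807 = 0.5865
- Null standard error: √(0.2425 × 0.0010544) = 0.01599; × 1.96 = 0.03134
- Alternative standard error: √(0.2475/1,300 + 0.24/3,507) = 0.01609
- (0.05 − 0.03134)/0.01609 = 1.16, so the chance of significance is about 88%

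Dividing both sample sizes by the variance inflation factor gives 60% at inflation 2 and 35% at inflation 4. This approximates the GEE analysis and does not simulate it.

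Sensitivity to the assumptions:

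- Non-treatment changes of 5% vs 10% in the remainder (Tier 2 of 52.5% vs 55%): 34% without clustering, 19% at inflation 2, 12% at inflation 4.
- Base rate 20% to 50% with 5 extra points: 87–96% without clustering, 59–73% at inflation 2, 34–44% at inflation 4.
- Same base rates with 2 to 3 extra points: 23–61% without clustering.

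**4. What the Tier 3 wording does to the same data**

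Keep the rates of step 3, take Tier 2 as in Table 2, and let a share s of every type of change be implemented, equal in both groups.

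- Table 2 wording, all patients: 0.55s vs 0.60s. Intervention looks better.
- Data collection wording, treatment among Tier 2 patients: 0.50s/0.55 = 0.909s vs 0.50s/0.60 = 0.833s. Intervention looks worse.
- Treatment started, all patients: 0.50s in both. No difference.

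One data set with identical treatment gives a gain, a loss or no difference.

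**The case against.** A care-process endpoint is legitimate here. The Trial design section declares a Hybrid Type 3 study, the primary endpoint is named as a change in patient management, and the abstract, Table 2 and the stated hypotheses all disclose that diagnostics count. Response, survival and toxicity have their own secondary endpoints, and the analysis section adds analyses by evidence level of the recommended therapies. Replacing the primary endpoint now would be a late change: recruitment closed on 30 September 2024, and data collection was due to end in November 2025. This stands, and it is why the composite need not be dropped. It does not close the gap, because the objectives are worded as treatment objectives and an analysis by evidence level does not take diagnostics-only or counselling-only patients out of the primary comparison.

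A reader might infer something stronger: that, because diagnostics and counselling referrals belong to the DNPM standard, the intervention group scores simply by delivering the intervention, so the comparison favours it by construction. The document does not support that.

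- The standard speaks of standardising diagnostics and referrals, not of increasing them. The project goals also mention preventing over-provision, so counts could fall.
- Control patients also qualify for a tumor board and receive site-specific personalized medicine. They can score by the same routes.
- Treatment recommendations in the tumor board are equally part of the standard, so the same argument would disqualify a therapy-only tier.
- For Tier 3, the data collection section requires treatment. It is therefore not established that Tier 3 can be met without it.

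The rates in the illustration are also assumptions. They show that the problem can occur, not that it is likely.

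**Conclusion.** The point holds in limited form. Tiers 2 and 3 as worded in Table 2 and the analysis section cannot by themselves show whether the treatment objectives were met. A Tier 2 difference, and on the Table 2 wording a Tier 3 difference, could arise with equal treatment recommendation and treatment rates. Whether it would, and in which direction, is unknown: the document gives no tier rates and does not say that certification raises the number of diagnostic or counselling changes. On the assumed rates, a purely non-treatment difference equal to the 5 points used in the sample size would be significant with probability about 88%, falling to 60% and 35% at variance inflation 2 and 4; smaller shifts matter less.

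The contradiction in the Tier 3 definition needs no assumption. The sections disagree on whether treatment is required, and only one of them restricts the denominator to Tier 2 patients. This is a cheap improvement, not grounds for rejecting the endpoint.

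**What to change.** Before analysis:

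1. Write one definition and one denominator for each tier, and use them in Table 2, the data collection section and the analysis section. State whether a counselling recommendation alone counts.
2. Add a prespecified therapy-only analysis with the same GEE model: Tier 2 as a changed therapy recommendation, Tier 3 as that therapy started. Name it as the analysis that answers the treatment objectives.
3. Report diagnostics-only and counselling-only changes by group as separate named components, and base any conclusion about treatment on the therapy component alone.

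The cost is wording and a little more analysis. The instrument is meant to record the original and new procedure and the extent of change, with molecular diagnostics and therapy as examples, and the health economic section relies on reported drugs and therapy modalities, so the therapy component should be derivable. That counselling-only patients can be identified is an assumption; no such field is shown, and the sponsor should confirm it. The downside is that the therapy-only proportions and difference may be smaller than those of the composite.
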